## Abstract

International evidence supports the effect of intensive family preservation and reunification services in preventing children’s placement in out-of-home care (OOHC). Evidence within Australia is scarce. This protocol paper describes a hybrid effectiveness-implementation evaluation of the Victorian Family Preservation and Reunification (FPR) Response implemented by MacKillop Family Services. Participants include families engaged in the program and staff involved in program delivery. A pre-post study design will be used to assess the effectiveness of the FPR in improving family outcomes from intake to closure, including: (i) parenting knowledge, skills, and capability; (ii) family safety and home environment; (iii) child development, adolescent behaviour, education attendance and attachment; (iv) connection to services; and (v) prevention of children from entering or re-entering OOHC. Interviews and focus groups will be conducted with staff to evaluate the program’s fidelity, reach, feasibility, acceptability, and enablers and barriers to implementation. Quantitative data will be analysed using descriptive statistics and a series of paired-samples t-tests and F tests to examine changes in outcomes over time; thematic analysis will be used for qualitative data. If the FPR can yield significant improvements in families’ outcomes, this would provide strong support for its scale-up across Australia, to better support vulnerable families.

## 1. Introduction

Intensive family preservation and reunification services are designed to keep children safe in the care of their parents and prevent child removal or subsequent placement into out-of-home care (OOHC; alternative accommodation when children cannot live at home safely [1]). They are effective in preventing children from entering OOHC 24 months post program engagement [2,3,4]. The effect of these programs is moderated by the sex and age of the child, parent age, the number of children and risk factors in the family, and practitioner caseload; greater effects (i.e., less OOHC placements) have been observed among families with boys and older parental age, whereas families with older and a greater number of children, single-parents, and higher caseloads were associated with reduced effects (i.e., more OOHC placements [5]). These programs have yielded additional positive outcomes for families, including reduced risk of maltreatment (particularly for high-risk families, [4]), and greater family functioning [5]. Finally, Tambling and Johnson (2020) concluded that increased provider-family contact (i.e., greater intensity of service) is associated with improved outcomes for families [6]. Despite these positive findings, additional primary research is required to establish a rigorous evidence base for intensive family preservation and reunification services, particularly in Australia where the literature is not well developed. Further, there is little known about how these programs work, the impact of parental adverse childhood experiences on current abuse and neglect [7] or the impact that person, social or environmental contexts have on the implementation of these programs [8]. These gaps in our understanding are a compelling rationale for the current study. This paper presents the study protocol of a mixed-methods evaluation of an intensive preservation and reunification program.

### 1.1. A Family Preservation and Reunification Services Program within One State of Australia

The Children Youth and Families Act 2005 gives a legislative basis for a system of services targeting vulnerable families [9]. In Victoria, it is the Department of Family, Fairness and Housing (DFFH) that runs child protection and investigates and manages the care of children with substantiated cases of abuse or neglect. In 2016, the Victorian government sought to review and reconstruct the service delivery system that engages children, youth and families following two royal commissions into: (1) child sexual abuse [10]; and (2) family violence [11]. The Roadmap for Reform: Strong Families, Safe Children [12] and the Roadmap to Recovery [13] are the blueprints used to restructure the system. The Victorian Family Preservation and Reunification Response (hereafter the Response, or FPR) is part of this restructuring to strengthen early intervention for disadvantaged families across the state and prevent/reduce OOHC placements [14].

In June 2020, a tender was put out requesting submissions from suitable community service organisations across Victoria who deliver family services to vulnerable families. Seventeen tenders were released to deliver the program across sites in both urban and regional settings. The goal of the Response was stated as being “strong families-with children who are safe, healthy, resilient and thriving; and parents who are supported to create a safe and nurturing home environment” [15]. The program seeks to provide intensive support to families where the children are at significant risk of being removed and placed in OOHC, or to enable the reunification of removed children in a timely manner. Referrals into the program are made via Child Protection, yet participation is voluntary. The FPR model is premised on the assumption that early, targeted and intensive support will permanently change the trajectory of vulnerable families away from the child protection (CP) system and towards the self-management of needs. OOHC placement often has adverse impacts on the child and family, and is extremely costly [16]. Hence, from a social, emotional and economic perspective, it is much better if families are supported and strengthened to ensure children can stay at home, safely. Table S1 outlines the government-led, individual core components of the Victorian FPR Response. Many are unique compared to other intensive family services by, for example, targeting adolescents, having a focus on implementation science (i.e., exploring *how* the program is being delivered), significant brokerage (i.e., funding to be used to purchase necessities for the family, such as groceries, housing appliances, contribute to rent, medication etc) and a new role within child protection called a Navigator. The Navigator is a government position that has been established within child protection to ensure that coordinated, targeted, appropriate, and culturally safe referrals are made into the FPR program. Rather than being prescriptive in program design, the Victorian government allowed all community service organisations to propose their own version of the FPR Response (within some broad parameters), with the view that consistency will be embedded through the government’s delivery of training and coaching to common practice elements (i.e., core components of program delivery) [17]. MacKillop Family Services was awarded nine areas of Victoria (six urban and three regional) to deliver the program.

### 1.2. The MacKillop Family Services FPR Program

MacKillop Family Services is a community service organisation that is committed to providing early intervention and family support services to disadvantaged families. Specifically, MacKillop strives to empower communities and families so that children can enjoy their childhood in a safe and loving home, can be healthy, thrive, and can develop to their potential. Key areas of intervention include operating foster care, residential care homes, homelessness support services, a suite of family service programs, specialist education services, and disability support and coordination services. In doing so, Mackillop supports children and young people to return to family, transition to independent living, heal from trauma, and to reconnect with learning and education. The FPR program aligns with MacKillop’s aim to provide early intervention for our most disadvantaged and vulnerable children, young people, and families. It addresses a key gap in the community—the lack of intensive family preservation and reunification services for high-risk and complex families. Therefore, the FPR program presents a significant opportunity to permanently change the trajectory of vulnerable youth out of the Child Protection system and OOHC, and capacity to breakdown the intergenerational cycles of maltreatment, OOHC placement, and disadvantage [15]. This protocol is necessary to outline and justify the program components, research processes, and measures being used in the evaluation.

The MacKillop FPR Response has eight core components in addition to the government’s key program guidelines. These include: (1) partnerships with other agencies to build expertise, local knowledge and networks; (2) embedding an independent evaluator; (3) utilising existing programs to incorporate into the Response; (4) extensive onboarding and training for staff; (5) being data-driven through assessment use to drive best practice; (6) a communities of practice for practitioners and team leaders; (7) organisational governance meetings; (8) suitable human resources to deliver the program and additional resources that enable program delivery with fidelity (i.e., as intended). More information about these components can be found in Table S2.

Families enter the program via the CP navigator. The navigator supports child protection practitioners to identify, engage, and connect the most appropriate families into the FPR program. Known as a ‘connection’ (i.e., referral or handover), the child protection practitioner, the Navigator, and MacKillop team leader discuss the family members, their circumstances, and past-history, prior to MacKillop accepting the family into the program. In alignment with collaborative practice and the two mandated Information sharing schemes (Child Information Sharing Scheme and Family Violence Information Sharing Schemes) [18,19], CP share all information relevant to the health and safety of the family and their workers. This includes mandated policy documents such as the Multi-Agency Risk Assessment and Management (MARAM) family violence screening and cultural support plans for Aboriginal and Torres Strait Islander children, as well as other known reports, such as mental health or disability assessments. Upon acceptance, MacKillop make contact within 48 hours and visits the family with CP within seven business days. These timeframes were prescribed by the Department of Family, Fairness and Housing. A thorough assessment of child and family outcomes is undertaken, and a ‘child and family action plan’ (i.e., care plan) is completed within 3 weeks that comprises the family’s goals, which are informed by those of CP. The plan is a living document that is revisited regularly to monitor progress and add or revise goals. CP workers are kept abreast of the family’s progress through attendance at care team meetings that are chaired by MacKillop Family Services workers.

The MacKillop key worker/practitioner engages with the family intensively, defined as a home visit for at least one hour, three times a week, or less visits and regular phone contact plus other activities as required. The timing of these visits is flexible to accommodate the needs of families. Funding is provided to allow for 200 hours of work with an additional 40 hours of step-down towards closure. It is expected that families will engage with the program for approximately six months, but this could last for up to a year. The most practical caseload per full time practitioner is four families, however workers may hold up to six families, albeit at a decreased intensity and with less fidelity to the model. In general, workers focus on reducing stressors and barriers to health and family functioning, such as housing, and offer referrals to specialist services if needed. Workers also focus on the interactions within the family and strengthen core life skills.

For families who are subject to an unborn report (reported to CP while pregnant) or with children aged 0–9, workers use evidence informed methods that focus on parenting skills (i.e., sleep settling, developing routines, responding to cues, use of consequences etc), parent–child attachment, and capacity to effectively respond during a crisis, such as those from the newborn behavioural observation method [20] or circle of security program [21]. These methods support families to meet their goals and mitigate risk. Specifically, the brokerage is a crucial component of the program that helps to fund items that meet families’ immediate or essential needs (i.e., groceries, rent), or can support families to achieve their goals (i.e., fund mental health or substance use counselling). As participation is voluntary and no specific incentives are provided, the brokerage may often be viewed by families as an incentive to engage in the program.

The program is also designed to support families to link into the community and its services to build independence, self-sufficiency, and a social network. Multi-disciplinary teams forged through partnerships with other agencies enhances the direct engagement of families with experts in parenting, drug and alcohol services, as well as regional care. Once families are better placed to meet the challenges they face and preferably with achieved goals, MacKillop will close the connection, but not before they provide the families with referrals to other programs or services if needed. For some families with young children, and where agreed to by the CP Navigator, an additional episode of care (240 h) will be provided to ensure that the family’s capacity is sufficient to keep children safe and thrive.

Families in metropolitan areas with young people aged 10–17 years engage with the evidence based Multi-Systemic Therapy Psychiatric (MST-Psych) program [22,23] where they see a trained MST-Psych MacKillop worker (termed family therapist) for at least one hour, three times a week. Full time family therapists are expected to hold up to four families and be available after hours where necessary. Family therapists adopt a systems approach by working closely with the child as well as the systems in which they live, e.g., caregiver, broader family members, home environment, school, peers, and community. They implement a range of evidence-based interventions, such as behavioural therapy, parent management training, cognitive behavioural therapy, and family therapy to meet the treatment goals within each system before closure. The regional MacKillop FPR programs also work with families of this age group, however they do not deliver an approved MST-Psych program, rather, they offer a service informed by this expertise.

Due to the lack of Australian evidence regarding the impact of intensive family preservation and reunification programs, a comprehensive mixed-methods evaluation of the MacKillop Family Services FPR program is being undertaken. In order to determine the effectiveness of the program, outcomes including parental knowledge, parenting skills, and capability; child development, adolescent behaviour and education attendance; connection to and use of family services; and protection from child abuse and neglect, were chosen in consultation with key stakeholders. These outcomes are associated with healthy, resilient and thriving children, and the work of family preservation and reunification programs [2,5]. Familial complexity, OOHC experience, and trauma, are risk factors for child abuse and neglect, which is under measured in current preservation programs [7]. These are being assessed to understand the factors that support program delivery. In addition to the assessment of effectiveness in relation to child, parent and family outcomes, the implementation of the FPR program is also being evaluated to inform future scale up [3,8].

### 1.3. Aim and Research Objectives

The overall aim of this paper is to outline MacKillop Family Services’ delivery of the FPR across nine sites and provide the research protocol for the three-year study period (October 2020–October 2023). This evaluation focuses on both parent/caregiver (hereafter parents) and child outcomes in relation to the effectiveness of FPR, and also seeks to evaluate the barriers and enablers, feasibility, fidelity and reach of the FPR program during the delivery and implementation phase.

Research objectives:To use reliable and valid measures to assess the effectiveness of the FPR through changes in the following parent and child outcomes: (i) parenting knowledge, skills, and capability over time; (ii) family safety and home environment; (iii) child development, adolescent behaviour, education attendance and parent/child attachment; (iv) connection of parents to services; and (v) prevention of children from entering or re-entering the OOHC system over a long-term period (12 months).To examine the implementation of the FPR by investigating the following outcomes: (i) the acceptability, appropriateness and feasibility of the program from the perspective of parents and staff; (ii) determine if the model can be implemented with fidelity (i.e., delivered as intended); (iii) evaluate the readiness of families to engage with the program, including reach; and (iv) examine the process, barriers and enablers of program delivery.

In addition to these research objectives, parental history of adverse childhood experiences and OOHC participation are being examined as risk factors contributing to current child abuse and neglect in response to recent gaps in the literature (Landers et al., 2018).

## 2. Materials and Methods

This paper was written using the Standard Protocol Items: Recommendations for Intervention Trials (SPRIRT) framework (2013) for writing protocol papers (see Table S3). The protocol was registered with Australian New Zealand Clinical Trials Registry (ANZCTR, 382402) and aligns with the World Health Organisation’s Trial Registration Data Set. Any changes made to the protocol will be communicated to the relevant parties (for example, investigators, ethics committee, trial registry and so on).

### 2.1. Ethics

Approval was obtained from the Monash University Human Research Ethics Committee to undertake the research study. MacKillop Family Services also reviewed and approved this research.

### 2.2. Study Design

This study aims to investigate the effectiveness and implementation of the FPR concurrently. To do so, this study adopts a mixed-methods study design involving a longitudinal single group pre-post study design combined with qualitative components. Given that participants are at high risk of child removal, it is not possible to include a control group, and a waitlist or similar group are also not viable. Other alternative study types are also not suited (for example, interrupted time series [24], because we cannot track participants for extended and lengthy periods of time). That is, given that the program’s duration is brief (200 h), highly intensive, and has a unique mix of outcome measures, any possibility for a matched control group regardless of prospective or retrospective data collection is prohibited. For these reasons, a quasi-experimental pre-post study design is being used to evaluate the effectiveness of MacKillop’s FPR program, acknowledging there are limitations to this approach. A multi-methods approach to data collection is being utilised, including focus groups, interviews, surveys, assessment questionnaires, and document analysis. Information from parents is being obtained only from those who provide consent. The study sites include all nine regions across Victoria, Australia, where MacKillop delivers the FPR.

### 2.3. Participants

There are two participant groups in this study: parents and MacKillop Family Services staff.

Parents: Parents either have children (0–17 years of age) who are vulnerable to removal from the home due to a child protection assessment of risk, have children already in OOHC, or are pregnant and have had ‘unborn’ reports to child protection. These parents may have multiple factors that are contributing to their risk profile including recent family violence, drug or alcohol misuse, fragile mental health, court orders and justice involvement among others. Parents can vary in age and may be adolescent parents or those who are currently living in a care arrangement (foster, kinship, or residential OOHC). Sample size calculations have been conducted using G*Power based on the NCFAS as this measure goes across most efficacy outcomes. For an analysis of variance test with the alpha set at 0.005, correlations between repeated measures set at 0.50 and power of 0.95, a total sample of 98 families will be required. To allow for a 25% rate of non-completion, at least 123 families will be recruited. During the study period, it is expected that up to 1100 families will engage in MacKillop’s FPR program. Based on similar research, we expect a high number of families to consent to participate in the study [25], therefore, it is expected that this sample size requirement will be met by the end of the study period.

MacKillop Family Services Staff: MacKillop directors, managers, team leaders and practitioners involved in the delivery of the FPR program are eligible to participate in interviews or focus groups about their experiences of implementing the program. Only staff who consent will take part in the research evaluation.

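### The minimum of 123 families comes from multiplying 98 by 1.25 rather than dividing by 0.75, so it covers about 20% non-completion, not the stated 25% (minor)

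*Protocol article*

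**What the plan says.** Section 2.3 (Participants) of the protocol article gives the sample size in consecutive sentences. The basis is stated as "Sample size calculations have been conducted using G*Power based on the NCFAS". The test and its settings follow: "For an analysis of variance test with the alpha set at 0.005", with "correlations between repeated measures set at 0.50 and power of 0.95". The result is that "a total sample of 98 families will be required". The allowance for loss comes next: "To allow for a 25% rate of non-completion, at least 123 families will be recruited".

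The same section expects up to 1100 families to engage in the program, anticipates a high consent rate, and expects the requirement to be reached by the time the study period ends. No other part of the article gives a different recruitment target or defines the 25% in another way. No effect size is given.

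**The concern.** Three figures stand side by side: 98 required, 25% lost, 123 recruited. They do not fit together. A rate of non-completion is naturally a share of the families who start, so the number recruited has to be large enough that 75% of it is still 98. Adding 25% of 98 to 98 does not achieve this, because the 25% is then lost from the larger number.

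What is at stake is whether the stated minimum does what its sentence says it does. A team that checks recruitment against 123 would believe the allowance for 25% loss was in place when only about 20% is covered. The power attached to 98 would then be slightly overstated for a study that recruited exactly the minimum and lost a quarter of it.

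**Working it through.** **Inputs.** All are from section 2.3 unless noted.
- Required number: 98 families.
- Non-completion: 25%.
- Stated minimum to recruit: 123.
- Alpha 0.005, correlation between repeated measures 0.50, power 0.95.
- NCFAS-GR occasions: three (start, middle, closure), from section 3.1.1.
- Effect size: not stated, so treated as an assumption below.

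**Step 1: reproduce the stated figure.** 98 × (1 + 0.25) = 122.5, rounded up to 123. This matches exactly.

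**Step 2: what 123 delivers at 25% loss.** 123 × (1 − 0.25) = 92.25, so about 92 completers. The shortfall is 98 − 92 = 6 families, or 6/98 = 6%.

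**Step 3: the loss that 123 does cover.** 1 − 98/123 = 0.203, or 20.3%.

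**Step 4: the minimum that covers 25%.** 98 / (1 − 0.25) = 130.67, rounded up to 131. Check: 131 × 0.75 = 98.25, which meets 98 in expectation, whereas 130 × 0.75 = 97.5 does not. The difference from the stated minimum is 131 − 123 = 8 families.

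**Step 5: effect on power.** For a one-group repeated-measures ANOVA with N families, m occasions, correlation ρ and effect size f, the noncentrality is λ = N·m·f² / (1 − ρ), with m − 1 and (N − 1)(m − 1) degrees of freedom. Because f is not stated, it was solved so that 98 families give exactly the stated 0.95 at alpha 0.005 and ρ = 0.50. Power was then read at 92.

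| Occasions | f that gives 0.95 at N = 98 | Power at N = 92 |
|---|---|---|
| 3 | 0.1995 | 0.9325 |
| 2 | 0.2295 | 0.9333 |

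With the round value f = 0.20 and three occasions, λ = 98 × 3 × 0.04 / 0.5 = 23.52 and power is 0.951 at 98. At 92, λ = 22.08 and power is 0.934. Every route gives a fall from about 95% to about 93%.

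**Step 6: how much rests on the assumed effect size.** Over f from 0.10 to 0.40, the N needed for 0.95 power runs from 383 down to 27 with three occasions, and from 500 down to 35 with two. A match at f = 0.20 therefore does not show which effect size the protocol used. Steps 1 to 4 do not depend on it, since they take 98 as given. Step 5 is conditional on 98 giving 95% power.

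**The case against.** The strongest reply is that the slip is real but hardly matters. Several parts of it stand.

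- **123 is a floor.** The wording is "at least 123 families will be recruited". Section 2.4 has all parents in the program invited, section 3 has the data of consenting families included, and section 1.3 fixes the period at October 2020 to October 2023. Enrolment looks limited by time rather than by a count. If the program reaches 1100 families, 123 needs 123/1100 = 11.2% to consent and 131 needs 131/1100 = 11.9%. The 1100 is an upper expectation and the consent rate is unknown, so this does not prove that 131 will be reached. It does make the 8-family difference unlikely to decide the final sample.
- **The power loss is about two percentage points**, at a strict alpha of 0.005. No planned estimate or test changes.

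A reader might infer more than the document supports:

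- *That the study will end with 92 completers.* This follows only if recruitment halts at exactly 123 and loss is exactly 25%.
- *That recruitment may be closed at 123.* No rule in the article says so.
- *That about 31 families would lack closure data.* Non-completion is not defined as a missing closure assessment. The NCFAS-GR is completed by the worker at closure (section 3.1.1), and Table 1 separates families who finished the program from those who closed early. A family that did not complete may or may not have a closure score.

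What does not survive is the idea that 123 might be right as it stands. That would need the 25% to be a share of completers rather than of those recruited, and nothing in the article says so.

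**Conclusion.** The recruitment minimum is wrong on the protocol's own figures. It was obtained by multiplying by 1.25 where dividing by 0.75 was needed. At the stated minimum and the stated non-completion, 6 of the required 98 families are missing.

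This is a minor correction. The finding about the target rests only on 98, 25% and 123, with non-completion read in the ordinary way as a share of families recruited. The power figure of about 93% rests in addition on the unstated effect size being whatever makes 98 give 95%. It does not support calling the study underpowered or predicting its final sample.

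**What to change.** Change one sentence in section 2.3, in any of three ways:

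1. State the minimum as at least 131 families (98 / 0.75).
2. Keep 123 and say that it allows for about 20% non-completion.
3. Keep 123 and 25%, and say that recruiting the minimum would yield about 92 completers and roughly 93% power, provided the calculation behind 98 holds.

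The first is the cleanest, because it keeps both the required number and the assumed loss. It raises the minimum by 8 consenting families. Section 3 says the assessments are already part of standard practice for all families in the program, so no new data collection is needed. The other two options cost only the rewording.
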